### STATISTICAL PLAN:

The primary objective of this study is to evaluate the molecular effects of soy isoflavones on human prostate cancer as well as the effects on serum androgen and estrogen levels. The goal is to randomize a total of 86 patients (43 to the control/placebo arm and 43 to the treatment/240mg soy arm). We will use a placebo and the lab personnel as well as clinicians, nurses and study coordinators will be blinded to treatment arm.

Randomization

Patients will be sequentially randomized into one of the two arms. Random permuted block randomization will be utilized. An independent statistician will generate the codes and will provide a copy of them to the VA research pharmacy. The study coordinator will notify the research pharmacy of the subjects ID number and the pharmacy will prepare the medication and distribute it to the patient.

Data Management

Two versions of an Access database will be created that mimics the patient data collection forms. One will be called primary and the other verification. Data will be entered into each database and then compares will be run to ensure the number of patients in each database is identical and that each data item is identical. This will be done each time data is to be entered. Logic, edit and range checks will be performed after compares have shown that the data in the primary and verification databases are identical. After the final patients data have been entered, compared and all logic, edit and range checks have been complete the database will be locked and data analysis will begin.

Sample Size and Power

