Two primary endpoints for specific aim 1 are total serum estrogen and testosterone. The goal is to determine if there is a difference in the change in these values between the two groups. Each of these endpoints will be tested at the 0.025 level of significance. Data from the pilot study indicated that total serum estrogen reductions will be 0 and 47 in the control and treatment arm respectively, with a common standard deviation of 36. From the same pilot study we expect that serum testosterone reduction will be 0 and 1.36 for the control and treatment arm respectively, with a common standard deviation of 2. Given this information, we want a sufficient sample size to have at least 80% power to detect these changes for both endpoints at the 0.025 level of significance. Using a two-sample t-test, 43 subjects per group will give us over 95% power to detect the expected difference in estrogen and 80% power to detect the expected difference in testosterone.

Statistical Analysis Plan:

Categorical demographic variables and baseline characteristics will be summarized by frequencies and percentages, overall and by group. Quantitative demographic variables and baseline characteristics will be summarized by means and standard deviations, overall and by group. For specific aim 1, the primary endpoints are total estrogen and testosterone. We will summarize baseline, post-treatment and change for these variables by means and standard deviations for both groups. We will then compare the change in each of these endpoints using a two-sample t-test, at the 0.025 level of significance. Similar procedures will be done on the other serum endpoints; estradiol, PSA, 5-DHT, IGF-1, and IGFBP-3, however, these tests will be at the 0.05 level of significance.

In an exploratory manner, we will use general linear models to determine if some or any of the baseline characteristics are predictive of change in these variables while controlling for treatment. We will also use Pearson’s correlation to determine if changes in the biomarkers are correlated with one another. For specific aim 2, the primary endpoints are ER-α and ER-β. Similar analyses to what was used for specific aim 1 will be applied to these endpoints as well at the 0.05 level of significance.

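### Aim 2 tests its two primary endpoints, ER-α and ER-β, at an unsplit 0.05, while Aim 1 splits alpha between its two, so false-positive error within Aim 2 can approach 10%

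*Protocol*

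**What the plan says.** All of the relevant text is in the Statistical Plan of the Protocol.

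- **Primary objective (opening paragraph).** Molecular effects and hormonal effects (the latter being those on androgens and estrogens in serum) are named together: "The primary objective of this study is to evaluate the molecular effects of soy isoflavones on human prostate cancer as well as the effects".
- **Aim 1 (Sample Size and Power).** "Two primary endpoints for specific aim 1 are total serum estrogen and testosterone". The plan then sets the level for the pair: "Each of these endpoints will be tested at the 0.025 level of significance". The analysis subsection repeats 0.025 for these two and puts the remaining serum markers at 0.05.
- **Aim 2 (Statistical Analysis Plan, last paragraph).** "For specific aim 2, the primary endpoints are ER-α and ER-β". The next sentence sets the method and level: "Similar analyses to what was used for specific aim 1 will be applied to these endpoints as well at the 0.05 level of significance".

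For Aim 2 the plan does not divide alpha or order the two tests. It does not say whether success needs one receptor or both. It also does not make the Aim 2 tests conditional on Aim 1.

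**The concern.** The two aims have the same structure, two endpoints both called primary, but only one pair is protected against testing twice. For the serum pair the plan accepts that two chances at a primary claim call for 0.025 each. For the receptor pair it uses the level that it gives to the non-primary serum markers.

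Under the plan as written, one receptor at p = 0.04 would meet the stated criterion for a primary endpoint, while testosterone at p = 0.04 would not. A result in one receptor only is foreseeable: of the two rat studies described in the Introduction, one reports down-regulation of one receptor subtype but not the other. A reader of the trial report would expect a claim on a primary endpoint to carry about a 5% error rate for its aim, and Aim 2 does not provide that.

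**Working it through.** **1. Reproduce the plan's own figures, to confirm what 0.025 means.** Inputs from Sample Size and Power: 43 per arm; for estrogen, "total serum estrogen reductions will be 0 and 47 in the control and treatment arm respectively, with a common standard deviation of 36"; for testosterone, "serum testosterone reduction will be 0 and 1.36 for the control and treatment arm respectively, with a common standard deviation of 2". Two-sample t-test, 84 degrees of freedom, noncentrality = (difference/SD) × √(n/2), with √(43/2) = 4.637.

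| Endpoint | Difference/SD | Noncentrality | Power, two-sided 0.025 | Plan states |
|---|---|---|---|---|
| Testosterone | 1.36/2 = 0.680 | 3.153 | 80.6% | 80% |
| Estrogen | 47/36 = 1.306 | 6.054 | above 99.9% | over 95% |

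The n needed for 80% power on testosterone is 42.4, hence 43 per arm. The plan does not state sidedness. A two-sided 0.025 reproduces its figure, whereas a one-sided 0.025 would give 87.6% for testosterone. The Aim 1 sizing is therefore sound and uses a true split of a two-sided 0.05.

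**2. Family-wise error within each aim.** This is the probability of at least one rejection when both null hypotheses of the aim are true. For independent tests it is 1 − (1 − α₁)(1 − α₂), and it can never exceed α₁ + α₂.

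- Aim 1: 1 − 0.975² = 4.94% (bound 5%).
- Aim 2 as written: 1 − 0.95² = 9.75% (bound 10%).

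**3. Sensitivity to correlation.** The Protocol gives no correlation between the ER-α and ER-β changes, so the values below are assumptions. Pairs of correlated normal test statistics were simulated (1,000,000 draws), each tested two-sided at 0.05.

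| Assumed correlation | Aim 2 error |
|---|---|
| 0 | 9.7% (exact 9.75%) |
| 0.3 | 9.5% |
| 0.5 | 9.1% |
| 0.7 | 8.3% |
| 0.9 | 7.0% |

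The error exceeds 5% at every value tried. It would fall to 5% only if the two tests were perfectly correlated.

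**4. After a fix.** With 0.025 for each receptor, the Aim 2 error is 4.94% under independence and at most 5% otherwise. Holm's procedure also holds it at 5% or less.

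**The case against.** Several points can be made for the plan.

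- **The wording does not say each.** The Aim 1 sentence does; the Aim 2 sentence does not, so 0.05 could be read as a total. But Aim 1 spells out its per-test level, and the Aim 2 sentence follows the pattern used for the other serum markers, which are plainly tested one by one. Per-endpoint is the natural reading. If a total was meant, the plan gives no rule for dividing it.
- **The paragraph opens with exploratory work.** That phrase introduces the linear models for baseline predictors. The later sentence calls the receptors primary, and the opening of the Statistical Plan puts molecular effects in the primary objective.
- **No success rule is stated for Aim 2.** This stands as a condition. If both receptors had to succeed, 0.05 each would need no adjustment. The plan does not say so.
- **The receptors are probably correlated.** They are measured on slides from the same specimens. This stands, and it is why a range is given rather than 9.75% alone.
- **The study is an 86-patient, single-centre biomarker trial sized on Aim 1 only.** This stands, and it limits the severity.

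A stronger reading is tempting: pool all four primary tests (0.025, 0.025, 0.05, 0.05) and report a trial-wide error of 1 − (0.975²)(0.95²) = 14.2%, bound 15%. The documents do not support calling that a defect. The Objectives separate Aim 1, the clinical protocol, from Aims 2 and 3, the basic science, and each aim has its own hypothesis. Treating each aim as its own family is a defensible convention, and the Protocol promises no trial-wide 5%. A sound split within Aim 2 would itself leave 1 − 0.975⁴ = 9.6% (bound 10%) over the four tests. Testing all four at 0.0125 would cut testosterone power from 80.6% to 72.5%.

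**Conclusion.** The plan departs from its own rule. Two primary endpoints share a 0.05 in Aim 1, while in Aim 2 each, on the natural reading, receives the full 0.05. The false-positive rate within Aim 2 is then 9.75% under independence, at most 10%, and roughly 7.0% to 9.5% for assumed correlations of 0.9 down to 0.3. These figures assume that neither receptor changes under soy and that either one alone can support a claim.

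This should be fixed. It does not affect the Aim 1 tests, their stated power or the sample size. A reader might also infer that the trial as a whole fails to control its error rate; that does not follow unless the aims are treated as one family, which the Protocol does not do.

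**What to change.** Replace the Aim 2 sentence, before unblinding, with one that treats ER-α and ER-β as a single family at a two-sided 0.05. Either form works:

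- **Fixed split:** each receptor at 0.025, exactly as in Aim 1.
- **Holm:** the smaller p-value against 0.025 and, if it passes, the other against 0.05. If Holm is chosen it may be applied to the Aim 1 pair as well, so that both aims follow one rule. Holm rejects whenever the fixed split does, so the stated Aim 1 power is not reduced.

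It would help to add that each aim is its own family.

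**Cost.** No patients are added. A single-receptor result with p between 0.025 and 0.05 no longer counts as positive on its own. With 43 evaluable patients per arm (an assumption for the tissue endpoints), the standardised difference detectable with 80% power by a two-sided t-test rises from 0.61 SD at 0.05 to 0.68 SD at 0.025. Under Holm that loss falls only on the first receptor to be tested.

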1. CRITERIA FOR REMOVAL FROM STUDY
2. Progression of disease.
3. Resultant delay of surgery treatment greater than 3 weeks.
4. Unacceptable toxicity: there will be no dose reductions, any patient with unacceptable toxicity will be removed and proceed with planned prostatectomy.
5. The patient may withdraw from the study at any time for any reason.

1. HUMAN SUBJECTS:
2. **Risk of Subjects**

Human Subject Involvement and Characteristics: This study will involve patients who are scheduled to undergo radical prostatectomy for treatment of their prostate cancer. Patient will receive variable doses of a soy supplement from the time of study enrollment until the time of their planned surgery. All patients must have histologic confirmation of adenocarcinoma of the prostate must be surgical candidates as dictated by their disease stage and health status. Because of disease being studied, all patients will be males of all ethnic backgrounds who are greater than 18 years of age with the expected age range of 55-70. All patients must meet the following additional eligibility and exclusion criteria: a) patients must agree not to take any new vitamin supplementation or herbal remedy, b) must not be receiving concurrent chemotherapy, radiation or hormonal therapy, c) no history of prior allergy and intolerability to soy-based products, d) must not have been taking any soy supplementation or soy isoflavones within 90 days prior to study enrollment, e) must be able to safely be on supplements for period of at least two weeks prior to the scheduled prostatectomy, f) all patients must have been informed of the investigational natures of this study and must sign and give written informed consent in accordance with institutional and federal guidelines. A total of 86 patient will be accrued over a three-year period.

Sources of Materials: Sources of research material include serum, tissue specimens and clinical data which will include toxicity data and demographic characteristics. Serum will be collected at study enrollment, after two weeks, and at the time of prostatectomy. Prostate tissue will be collected at the time of the diagnostic biopsy and prostatectomy. All material will be collected specifically for research purposes.

Potential Risks: Although there was no toxicity seen in the pilot trial, the potential research risk of treating with an estrogenic agent includes an increase risk of thrombosis, gynecomastia, fluid retention and elevation of liver function tests. Based on preliminary data and prior studies, these risks are of low likelihood and readily reversible with the exception of thrombosis. Although it is of low likelihood, thrombosis can lead to fatal pulmonary embolism in a small percentage of case. Phlebotomy risks include pain at the injection site and infection. There are no known social, psychological and legal risks. Therapeutic risks include postoperative thrombosis, infection, impotency and incontinence which all can occur with a standard prostatectomy**.** The thrombotic risk is expected to be extremely with no risk reported in other published trials of soy supplementations.

1. **Adequacy of Protection for Risks**

Recruitment and Informed Consent: Potential patients will subjects who have been referred to the urology clinics at the VAMC for evaluation of a potential prostate cancer (elevated PSA, DRE) and have subsequent documentation of an invasive prostate cancer. Only patients who are surgical candidates and have chosen surgical as their treatment choice will be offered participation. Patient will be provided consent form, information on soy supplementation and study aims in lay language. Potential candidates will be identified by participating investigators ([name], [name], [name]) who will also answer questions and provide additional education on the study. Patients will be allowed to read and take the consent home. Final consent will be obtained by [name] (Research Associate). Copy of the informed consent will be submitted to the IRB and maintained in the patient record. The IRB the Kansas City VAMC has not authorized a modification or waiver of the elements of consent or its documentation. All clinical personal have had human subjects/informed consent training.

Protection Against Risk: All adverse effects will be reported to the institutional IRB and all toxicity will be graded according to the NCI Common Toxicity Criteria, Version 3.0(**http://ctep.cancer.gov)**. **{**The University of Kansas Data Monitoring safety board(DMSB) will oversee this trial. Their review includes data quality and timeliness, adherence to study protocol, informed consent procedures and adverse events. Any grade 3 or 4 adverse effect (SAE) will result in immediate discontinuation of soy supplement and removing from treatment protocol. SAE’s will be immediately recorded and reported to the KCVA human subjects committee and the DMSB.**}** If any thrombosis occurs, patients will immediately be removed from study and will be treated promptly using standard anticoagulation protocols. Interim analysis on toxicity data will be performed every six months to ensure no differences in risks are seen with the treatment compared to the control arm. Every effort will be made to protect patient confidentiality including; a) all data will be keep in a secured area, and b) patient information will be coded with the names of the patients kept in a locked file.

1. **Potential Benefit of the Proposed Research to the Subject and Others**

Risk/Benefit Ratio: Although the direct benefit to the participating such is low, there is a substantial potential benefit to society if this study can aid in identifying a potential approach to prostate cancer prevention. The risk and toxicities of this intervention are also expected to be very minimal.

1. **Importance of Knowledge to be gained**

Prostate cancer is an enormous health problem with over 200,000 new cases diagnosed and 30,000 deaths occurring each year in the US alone. If a preventive strategy or a new chemopreventive agent could prevent only 5% of prostate cancers, 10,000 patients each year would not have to suffer from this disease. The risks of the treatment intervention in this study are very low compared to the potential knowledge gained.

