Serum prostate specific antigen (PSA) remains the most commonly used marker for prostate cancer screening and evaluation of disease recurrence. *In vitro* experiments have demonstrated a decreased in PSA production in response to soy isoflavones.41,42 In a small clinical trial, however, 34 patients with an elevated PSA received a soy beverage for a total of 12 weeks with no significant effect on serum PSA levels observed.43 The small sample size and the lack of a control arm, though, limited the study. A recently published study evaluated the effects of a genistein-rich commercial supplement on serum PSA in 62 men with a histologically confirmed prostate carcinoma. The trial included patients with recurrence after prostatectomy (RRP)(9), after radiation therapy (17), after both radiation and RRP (6), after hormonal therapy (14), and patients receiving surveillance only (16). Of the 52 evaluable patients who had received at least six months of supplementation, one patient had PSA reduction of >50% and 8 had PSA responses that were <50%. PSA responses were seen preferentially in patients only receiving active surveillance with 8 of 13 patients having either a stable or decreasing level.44 The authors postulate that prior treatment may have affected genistein’s ability to concentrate in the prostate gland, thereby decreasing the therapeutic effect. Our proposed randomized study, which will evaluate a group of previously untreated patients, will further delineate the soy isoflavone effect on PSA levels, evaluate the dose relationship, and correlate these changes with the molecular effects on both normal and malignant prostate tissue.

There has been no significant toxicity reported with comparable soy supplementation doses in other studies and no toxicity was seen in a pilot trial performed at our institution.45,46 Soy supplementation has been demonstrated to decrease endogenous hormone levels such as free T3, DHEA and serum cortisol.47-49 Longer-term supplementation could lead to toxicity as a result of the chronic effects on these hormone levels but is unlikely in this setting of short-term supplementation. Potential estrogenic effects include an increase risk of thrombosis, gynecomastia, fluid retention and, rarely, elevation of liver function tests.

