# Experimental Design:

# This will be a two-arm randomized study comparing a placebo control arm to supplementation with a commercial soy supplement. The time of initial biopsy to the time the surgery scheduled is typically 2-4 weeks in normal setting. Patients will be treated for a minimum of two weeks and continue treatment until the time of their prostatectomy. A total of 86 patients will be randomized (43 patients/arm).

Supplementation with Soy Isoflavones:

Dose Levels:

Dose 0: No soy (Placebo).

Dose 1: Four Capsules Twice Daily (240 mg of total isoflavones).

Treatment: The commercial soy supplement to be used is *Flav-Ein* (3B’s LTD, Lexena, Kansas)*.* This product was chosen because it is a pure soy extract and the individual concentration of each soy isoflavone is closely equivalent to a soy-based diet. It is supplied in capsular form. Each capsule contains 560 mg of pure soybean extract and 100mg of a non-soy legume (see appendix). Each capsule contains approximately 30mg of total isoflavones. The placebo will consist of an equivalent capsule with only the 100mg legume additive and no soy supplement.

1. ELIGIBILITY/EXCLUSION CRITERIA:

All patients must meet the following eligibility and exclusion criteria:

1. Histologically proven adenocarcinoma of the prostate.
2. Surgical candidate for radical prostatectomy.
3. During time of study period, patients must agree not to take any new vitamin supplementation or herbal remedy.
4. Must not be receiving concurrent chemotherapy, radiation or hormonal therapy.
5. No history of prior allergy and intolerability to soy-based products.
6. Must not have been taking any soy supplementation or soy isoflavones within 90 days prior to study enrollment.
7. Must be able to safely be on replacement for period of at least two weeks prior to the scheduled prostatectomy.
8. All patients must have been informed of the investigational natures of this study and must sign and give written informed consent in accordance with institutional and federal guidelines.
9. **STUDY CALENDAR**

| REQUIRED  STUDIES | Study Enrollment | Two Weeks | Preprostatectomy |
| --- | --- | --- | --- |
|  |  |  |  |
| EXAM |  |  |  |
| History/PE | X | X | X |
| Weight | X | X | X |
| PS | X | X | X |
| Toxicity | X | X | X |
|  |  |  |  |
| SERUM# |  |  |  |
| PSA | X | X | X |
| Estrogen(total) | X | X | X |
| Estradiol | X | X | X |
| Testosterone | X | X | X |
| DHT | X | X | X |
| SHBG | X | X | X |
| IGF-1 | X | X |  |

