1. TISSUE AND SERUM COLLECTION

Laboratory Collection and Assessment:

PSA, serum testosterone, 5-DHT, total estrogen and estradiol levels will be assessed at baseline, at two weeks and prior to prostatectomy (Table I). These will be done using standardized assays at the KCVA clinical laboratory. Serum levels of IGF-1, IGFBP-3 and genistein will be drawn at baseline after two weeks of supplementation. Genistein levels will be measured in [name] laboratory by the method described below. IGF-1 and IGFBP-3 will be completed in [name] laboratory using a standard RIA assay (ALPCO Diagnostics). All samples will be drawn in the early AM and in the fasting state.

Tissue Collection:

For the immunostaining(ER-α, ER-β, apoptosis, proliferation, cdc-2, pcdc-2) and in situ hybridization studies(ER-α, ER-β , cdc-2, pcdc-2) 10 paraffin embedded slides from the diagnostic biopsy (pre-soy) and 10 paraffin embedded slides from the prostatectomy specimen (post-soy), will be obtained on all enrolled patients. These slides will be obtained after pathologic processing and, if needed, additional paraffin sections will be available. In addition, at prostatectomy and prior to pathologic processing, the urological surgeon will obtain core samples of both adjacent normal prostate and tumor from each specimen. This tissue is collected in the operating room suite. Once collected, the samples are immediately snap frozen and stored in liquid nitrogen until experimental analysis. An H&E stained section will be obtained from each core to ensure the presence of tumor or adjacent normal tissue. This method of tissue collection has previously been reported59 is currently being successfully utilized at the Kansas City VAMC.

Genistein Levels and Specific Methods:

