#### Tissue and Serum Banking:

#### All patients will have a 15 ml red top drawn at enrollment, at two weeks and at the completion of soy supplementation. From this, we will use a 1ml aliquot for genistein analysis and a 1ml aliquot IGF-1/IGFBP-3 analysis. The remaining sample will be labeled and stored in –700C. Our studies will also require one tissue core of tumor and adjacent normal tissue. When feasible, at least one additional core of both tumor and normal tissue will be collected according to the tissue collection methods listed above. Samples will then be labeled and stored in liquid nitrogen. These samples will be available for additional investigation including potential future collaborative efforts. The KCVA is also one of the sites selected for the planned VA tissue and biorepository project and these samples could readily be contributed to that tissue bank.

####

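### Liver-test elevation is a named risk of the supplement, but no liver test is scheduled, so an elevation without symptoms cannot be graded or compared between arms through protocol procedures

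*Protocol*

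**What the plan says.** The risk is named twice. The Introduction states: "Potential estrogenic effects include an increase risk of thrombosis, gynecomastia, fluid retention and, rarely, elevation of liver function tests". The Human Subjects section, under Potential Risks, repeats the four items as "thrombosis, gynecomastia, fluid retention and elevation of liver function tests" and adds that "these risks are of low likelihood and readily reversible with the exception of thrombosis".

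The Study Calendar has nine serum rows: PSA, total estrogen, estradiol, testosterone, DHT, SHBG, IGF-1, IGFBP-3 and genistein. A typical row reads "Estrogen(total) | X | X | X", the three marks being enrollment, two weeks and preprostatectomy. There is no row for a liver enzyme, bilirubin or a liver panel.

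The Tissue and Serum Collection section follows the same list: "PSA, serum testosterone, 5-DHT, total estrogen and estradiol levels will be assessed at baseline, at two weeks and prior to prostatectomy", followed by IGF-1, IGFBP-3 and genistein. Under Tissue and Serum Banking, a 15 ml tube is drawn at all three time points. One 1 ml aliquot goes to genistein and another to the IGF assays, and then "The remaining sample will be labeled and stored in" the freezer. The toxicity paragraph in Efficacy and Safety Measurements gives visit times and the NCI version 3.0 criteria but no laboratory component.

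Under Protection Against Risk, all toxicity is graded by those criteria, "Any grade 3 or 4 adverse effect (SAE) will result in immediate discontinuation of soy supplement", and toxicity data are compared between the arms every six months.

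**The concern.** Three of the four named risks (thrombosis, gynecomastia and fluid retention) can show themselves clinically, and the calendar has history, physical examination and weight at every visit. The fourth is by definition a laboratory result. Without a blood test there is no value to grade unless the man has symptoms.

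Two safety provisions depend on that grade: the discontinuation rule for grade 3 or 4 effects, and the six-monthly check that the arms do not differ in risk. For an asymptomatic elevation, a site that follows the plan exactly has nothing to feed into either. With no baseline value, a result that turned up by chance could not be classed as new or pre-existing. At the end, an absence of recorded liver toxicity could not be read as evidence that none occurred.

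**Working it through.** **1. Matching each named risk to a scheduled assessment**

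| Named risk | Scheduled assessment that could reveal it |
| --- | --- |
| Thrombosis | History and examination, toxicity review (if clinically apparent) |
| Gynecomastia | History and examination, toxicity review |
| Fluid retention | Weight, history and examination, toxicity review |
| Liver-test elevation | No laboratory test; history, examination and toxicity review only if symptoms or signs occur |

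The last row follows from reading the Study Calendar, the toxicity paragraph, the laboratory section and the banking section together. None adds a safety chemistry. The eligibility list has no liver criterion and asks for no baseline liver value. The number of scheduled liver measurements is 0 at each of the three visits.

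**2. Following an asymptomatic elevation through the safety rules**

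- Grading by the version 3.0 criteria needs a measured value. None is scheduled.
- The grade 3 or 4 rule needs a grade. None can be assigned.
- The six-monthly comparison by arm needs data from both arms. None are collected.

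**3. How often a case might be expected**

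The documents give no rate, so this part is illustrative. With n = 43 in the soy arm and an assumed true rate p per man, the chance of at least one case is 1 − (1 − p)^43 and the expected number is 43p.

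| Assumed p | Expected cases | Calculation | Chance of at least one |
| --- | --- | --- | --- |
| 1% | 0.43 | 1 − 0.99^43 | 35% |
| 2% | 0.86 | 1 − 0.98^43 | 58% |
| 5% | 2.15 | 1 − 0.95^43 | 89% |
| 10% | 4.3 | 1 − 0.90^43 | 99% |

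The formula is the same whether p means any elevation or grade 3 or 4 only. The latter is a subset, so its p cannot be larger. Given the Introduction's description of the risk as rare, the upper rows should be read with caution.

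**4. Check that the main analysis is untouched**

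The plan states no figure on liver monitoring. Its only power statement (Sample Size and Power) reproduces: with 43 per arm and two-sided alpha 0.025, a difference of 47 with SD 36 gives 99.99% power, and 1.36 with SD 2 gives 80.6% by the noncentral t distribution, against the stated figures of over 95% and 80%. Neither depends on liver tests.

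**5. Number of assays**

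All three visits: 86 × 3 = 258. Baseline and one on-treatment visit: 86 × 2 = 172.

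**The case against.** **The risk is minor by the protocol's own account.** It is described as rare, of low likelihood and reversible, no toxicity was seen in the pilot, and exposure is short: biopsy to surgery is typically two to four weeks, with at least two weeks of capsules. This stands as a limit on importance. At 1% the expected count in the soy arm is below one, and a comparison of grade 3 or 4 events by arm would carry little information. It does not remove the gap. The Patient Accrual section reports only 13 men enrolled in the pilot, and the six-monthly review exists to check such expectations.

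**Liver toxicity is not wholly invisible.** A reader might infer that the plan cannot detect it at all. The documents do not support that. History, examination and toxicity review take place at each calendar visit, with a further toxicity check after surgery, and a monitoring board reviews adverse events. A symptomatic case could be recorded. Tests done in routine care might also reveal one, although the protocol neither requires nor collects them.

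**The discontinuation rule is not contradicted.** A reader might also infer that leaving an undetected case on capsules breaches that rule. It acts on effects that are observed and promises no laboratory surveillance, so no two sections conflict. What is missing is the measurement that would let the rule operate for this risk.

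**Clinicians may screen anyway.** Eligibility requires men to be fit for surgery and able to take the product safely for two weeks or more. That leaves room for judgement but requires no liver value.

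**Silent thrombosis would also be missed.** This is correct. The difference is that thrombosis can present clinically, whereas the fourth risk is named in the protocol as a laboratory abnormality.

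**Conclusion.** The point holds for asymptomatic elevations. One of the four risks the protocol names is defined by a laboratory result and has no scheduled measurement at any of the three visits. The grading, the grade 3 or 4 rule and the six-monthly comparison therefore cannot act on it through protocol procedures. A schedule of assessments is protocol content, and a separate analysis plan could not analyse values that were never collected.

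The size is uncertain. Across assumed true rates of 1% to 10%, the chance of at least one case among 43 soy-arm men runs from 35% to 99%. It would be tempting to quote the 89% for a 5% rate alone, but nothing in the documents supports that rate over the lower ones. The conclusion does not depend on which rate is right.

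This is a gap in safety monitoring that should be closed. It leaves the primary endpoints, alpha and sample size as they are.

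**What to change.** Reconcile the Study Calendar with the risk named in the Introduction and under Potential Risks. Add a liver-panel row at visits where blood is already drawn, at least at baseline and once on treatment. Run it on fresh serum before the remainder is frozen, grade it by the version 3.0 criteria already adopted, and include the results in the six-monthly toxicity table. Handling of abnormal results stays with the sponsor's clinicians under the existing rules.

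The KCVA clinical laboratory already runs PSA and hormones at all three visits, so no new visit or venepuncture should be needed. The cost is 172 to 258 routine assays and an added sample-handling step. The calendar footnote describes the serum as collected and stored, and the tube must also serve the other assays, so the site should confirm that the volume and timing work.

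There will be some incidental abnormal results. A few, in either arm, may lead to removal from treatment under the existing rule. The sponsor should weigh that, because 80% power for testosterone needs 42.4 men per arm by the t calculation and 43 are planned.
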